**Methods**

**Intervention:** The intervention will be based on a successful pilot program conducted by the research team that in turn was based on current evidence for the management of adolescent obesity [11, 30-31] and the successful “Fitmatters” program conducted in a tertiary clinical setting. Key strategies of the intervention were: focus on healthy behaviours rather than weight management, multi-disciplinary facilitators and family involvement. The intervention also focussed on the psychosocial aspects of being overweight and was based on to the families’ readiness to change using the PRECEDE-PROCEED Framework [32-35]

The program consists of an 8 week multi-disciplinary family-centred intervention focussed on improving activity, food and attitude habits. Groups of up to 12-15 adolescents and their parents attended 2 hour sessions twice weekly. On each occasion adolescents participated in a 45 minute exercise class involving aerobic, strength and coordination stations. Adolescents also participated in education sessions covering moderate physical activity, sedentary behaviours and diet. Tailored feedback on fitness, screen time and diet were provided to each adolescent. Other sessions provided support and group counselling on setting goals, overcoming set-backs and dealing with cognitive and emotional issues. Adolescents were set ‘homework’ relevant to the stage in the program – for example keeping a diary of TV programs watched. Parents participated in education sessions covering the same issues as the adolescents, sometimes with their child and sometimes separately. Parents also gained informal support from other parents and staff in ‘walk and talk’ sessions, which itself modelled a way of building more activity into their day. Parents were also given practical training in buying and preparing healthy food during a supermarket visit and cooking classes. All sessions were run during school term but out of school hours. A brief program outline is shown in Table 1 (each week has two rows – one for each program day). We intend to include regular contact (SMS, phone, mail) to assist motivation and maintenance of effects after the 8 weeks.

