# Study design: A wait-list controlled, staggered-entry cohort design will be used. Participants will be recruited and given an initial assessment then reassessed after 3 months waiting (just before starting the program). The dual pre-participation assessments will provide a within-subjects control period. Follow-up assessments will be conducted immediately after completing the program (3 months after second pre-program assessment) and at 3, 6 and 12 months post program.

Cohorts of 12-15 overweight adolescents and their parents will be progressively recruited over the study period. Cohorts are expected to start in Perth metropolitan October 2011, February 2012 and April 2012. The staggered start will control for external seasonal and public event confounders to intervention effects.

Table 1. Project community engagement (*), implementation cohorts (shaded) and follow up assessments (x)

| **Cohort** | **2011** | | | | **2012** | | | | **2013** | | | |
| --- | --- | --- | --- | --- | --- | --- | --- | --- | --- | --- | --- | --- |
|  | 1/4 | 2/4 | 3/4 | 4/4 | 1/4 | 2/4 | 3/4 | 4/4 | 1/4 | 2/4 | 3/4 | 4/4 |
| South metro | * | * | recruit | waitlist | S1 | S2 | S3x | x | x | x | x |  |
| East metro | * | * | recruit | waitlist | N1 | N2 | N3x | x | x | x | x |  |
| Regional | * |  | * | * | recruit | waitlist | R1 | R2 | x | x | x | x |

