## Analysis plan

Process evaluation will use descriptive statistics and qualitative analysis.

Impact and outcome evaluation will use a multi-level mixed modelling approach for the hierarchical data collected over the one-year observational period (repeated measurements of individuals nested within families.) Estimates of change in outcomes over time periods will be adjusted for potential confounders of age, gender, maturation level, IRSAD and parental education levels. All change estimates will be presented as adjusted mean change with corresponding 95% confidence intervals. Non-normally distributed data will be appropriately transformed as necessary, and statistical models checked for unduly influential outliers. All data analysis will be performed utilising current statistical software (Stata/IC 10.1 for Windows, Statacorp).

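### The mixed model omits the program group of 12-15 in which treatment is delivered, so confidence intervals are too narrow for any outcome whose change is positively correlated within groups

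*Protocol*

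**What the plan says.** The Analysis plan section of the Protocol commits to a model: "Impact and outcome evaluation will use a multi-level mixed modelling approach for the hierarchical data collected over the one-year observational period". It then names the levels: "repeated measurements of individuals nested within families". Estimates are to be "adjusted for potential confounders of age, gender, maturation level, IRSAD and parental education levels", and "All change estimates will be presented as adjusted mean change with corresponding 95% confidence intervals". Group, cohort and site appear neither as a level nor as a covariate.

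The Intervention paragraph under Methods describes joint delivery: "Groups of up to 12-15 adolescents and their parents attended 2 hour sessions twice weekly". Exercise classes and education are shared, and "Other sessions provided support and group counselling on setting goals, overcoming set-backs and dealing with cognitive and emotional issues". Under Study design, entry is also by group: "Cohorts of 12-15 overweight adolescents and their parents will be progressively recruited over the study period". The same section relies on the timing of entry as a design feature: "The staggered start will control for external seasonal and public event confounders to intervention effects".

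The Sample size paragraph asks for 96 adolescents at post test and 124 recruited. It mentions no design effect or ICC.

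**The concern.** Adolescents in one group share sessions, peers and calendar time. The changes of two members of a group are therefore likely to resemble each other more than the changes of two adolescents from different groups. A model whose highest level is the family treats members of different families in the same group as independent. The family level cannot stand in for the group, because each group contains many families.

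The Protocol's own argument for staggered entry points the same way. Within one cohort, everyone's wait-list period and program period fall in the same calendar windows, so a seasonal shift moves all their contrasts together. It averages out over cohorts, not over individuals within a cohort. On that reasoning replication is partly at cohort level, while the model counts individuals.

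The intervals at stake are those for the primary impact measures (activity, sedentary time, fruit and vegetable serves, extras) and for maintenance at 3, 6 and 12 months. Intervals that are too narrow favour claims of benefit.

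**Working it through.** **The plan's own figure.** The 96 cannot be used to infer a hidden allowance for clustering. With an effect size of 0.2, 80% power and two-sided 5%, a paired comparison with 0.2 expressed in SDs of change needs ((1.960 + 0.842)/0.2)² ≈ 196.2, that is 197. How 96 was reached is a separate matter. Here it is taken as given.

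**Inputs.** Group size m = 12 to 15 (Methods; Study design). Post-test n = 96 (Sample size). The ICC of change within a group is not in the Protocol; 0.01-0.10 is an assumption. Two-sided 5% is also assumed, because sidedness is not stated.

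**Formulas.** Design effect DE = 1 + (m − 1) × ICC. The interval should be √DE times as wide. Effective n = 96/DE. True error of a nominal 5% test = 2 × [1 − Φ(1.96/√DE)].

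For m = 12:

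| Assumed ICC | DE | √DE | Effective n | True error, formula | True error, simulated |
|---|---|---|---|---|---|
| 0.01 | 1.11 | 1.05 | 86.5 | 6.3% | 6.4% |
| 0.02 | 1.22 | 1.10 | 78.7 | 7.6% | 7.7% |
| 0.05 | 1.55 | 1.24 | 61.9 | 11.5% | 11.3% |
| 0.10 | 2.10 | 1.45 | 45.7 | 17.6% | 17.5% |

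The simulation used change scores for 8 groups of 12, with 20,000 runs per ICC and groups ignored in the analysis. With ICC 0 the error was 5.0%. A t interval on the eight group means covered 94.8% to 95.2% throughout, but the groups were generated as independent of each other.

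**Sensitivity to group size.** For m = 15, DE is 1.14-2.40 and the error 6.6%-20.6%. If 30% attrition thins groups of 12 to 12 × 0.7 = 8.4, DE is 1.07-1.74 and the error 5.9%-13.7%.

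**Why a group random intercept is not enough.** The impact contrast is program-period change minus wait-list change: (Y2 − Y1) − (Y1 − Y0) = Y2 − 2Y1 + Y0. A constant group effect has coefficient 1 − 2 + 1 = 0 and drops out. What inflates the variance is group variation in change, so the model needs a group-by-period term.

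**Number of groups.** The project table in Study design carries eight codes (S1-S3, N1-N3, R1-R2). Recruiting 124 in groups of 12-15 gives 124/15 = 8.3 to 124/12 = 10.3, and eight groups of 15 hold only 120. About 8-10 is what the Protocol supports.

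**Cost of the t reference.** With eight groups (7 df) the multiplier is 2.365 against 1.985 for 96 independent adolescents: 2.365/1.985 = 1.19. Combined with clustering: 1.05 × 1.19 = 1.25 to 1.45 × 1.19 = 1.73.

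**The case against.** The strongest reply concerns size. No ICC is given, and the outcomes range from accelerometer time to muscle force, motor competence and family functioning. A reader might infer that the error rate is exceeded for every outcome. The documents do not support that: it holds only where change is positively correlated within groups. The impact contrast also adds three occasions of individual measurement noise with weights 1, −2, 1, a variance multiple of 1 + 4 + 1 = 6. That dilutes a group effect acting only on response to the program, so the low end of the range may be nearer the truth for some outcomes. This stands.

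A reader might also infer that there are exactly eight groups with 7 degrees of freedom, or that a t-test on group means is sure to hold 5%. Neither is established. Eight is read from table codes and does not fit 124 recruits. By the same table, groups share sites (S1-S3; N1-N3) and quarters (S1 with N1, S2 with N2, S3 with N3 and R1), so group means may not be independent.

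Nor should the family level be dismissed as redundant. The section on parent outcome measures has parents completing several of the same questionnaires, so adolescent and parent can form a real family cluster.

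Last, random-effects detail is often left to a SAP, and none is at hand. That would answer a Protocol silent on structure. This one names its levels and covariates, and an analyst who follows it would leave out the level at which treatment is delivered.

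**Conclusion.** The point holds as a conditional one. For any outcome with positive within-group correlation of change, the planned 95% intervals are too narrow. With 12 per group and an assumed ICC of 0.01-0.10, the correct interval is about 1.05 to 1.45 times as wide before any small-sample correction, and the true two-sided error is about 6% to 18%. The direction follows from joint delivery and staggered entry as the Protocol describes them. The size rests on the assumed ICC and on groups of equal size; at ICC 0.01 it is small. It does not show that all outcomes are affected.

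**What to change.** In the Analysis plan:

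- Add program group as a level, with a random group-by-period effect so that change may vary between groups.
- Take small-sample degrees of freedom from the actual number of groups (about 8-10).
- Keep the family level wherever siblings or parent-adolescent pairs are modelled together.
- Add a sensitivity analysis on group-level mean contrasts that allows for shared site and calendar quarter.

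The only data needed are group membership, site and dates, which the trial will hold.

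The cost is precision. Intervals widen by roughly 5-45% for clustering and, with eight groups, by about 19% more for the t reference, about 25-73% in total. The 19% is paid even if the ICC is zero. The effective n of 86 to 46 out of 96 also means less power than planned, which the Sample size paragraph should acknowledge. To keep the information of 96 independent adolescents, 96 × 1.11 to 96 × 2.10, or 107 to 202, would be needed at 12 per group.

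The group-level analysis can only be a check. With eight groups in three sites and four quarters, fixed terms for both would leave 8 − 1 − 2 − 3 = 2 residual degrees of freedom, so site and quarter may have to be examined one at a time. It also gives up the planned individual-level covariate adjustment unless that is done first.
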